### Randomisation

Following consent and baseline data collection participants are allocated to the groups using block randomisation. This form of randomisation is recommended for large trials [29] and has been used in a number of recent trials in this research area [21]. A permuted block randomisation scheme with a random mixture of block sizes is used to set the allocation order, stratifying participants by hospital and presence of a dental problem. Block randomisation ensures that the number of participants in each arm of the trial will be evenly balanced [29]. Randomisation of participants is accomplished centrally using an independent computerised service which is accessed via the telephone at the time of recruitment.

Group allocation (IG1, IG2, CG) is represented by coloured stickers concealed in serially numbered opaque randomisation envelopes. After recruitment, baseline data collection and randomisation via telephone, the dental assistant hands over the randomisation envelope to the pregnant women, who then gives it to the midwife. All midwives at each of the hospitals are aware of which group each coloured sticker represents. To maintain allocation concealment and minimise selection bias the dental assistants are unaware of the colour codes and block sizes used for randomisation. In addition, the study investigators are blinded to group allocation. Due to the randomisation method, pregnant women attending on the same day receive different interventions.

To minimise any distress among pregnant women and maintain equipoise [30], oral health promotion material are provided via the dental assistant at recruitment to all trial participants. Women who refuse to participate are also provided with oral health promotional material. It is also possible that women attending the antenatal clinic on the same day might interact with each other which can lead to potential contamination (estimated at <5%) in the study. We are adjusting for this contamination during analysis [31] and have also included an item in the post questionaire asking if they have discussed their particpation in the study with other women attending the antenatal clinic at the same time. Analysis is being undertaken excluding such women.

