### Sample size

Sample size estimation is calculated on the outcome measure uptake of dental services using the assumption that 30% of pregnant women in the control group will access dental services during pregnancy (based on our survey [23] and existing Australian studies [10, 43, 44]. We expect the MIOH (IG1) and MIOH-DS service (IG2) will improve the uptake of dental services. The MIOH intervention is considered successful if at least 50% of the pregnant women in IG1 and IG2 will access dental services during pregnancy, a difference of 20% between the groups. To detect a difference of at least 20% between the groups with a two-sided test of proportions, alpha of 0.017 (three comparisons 0.05/3), and 80% power we determine using a statistical software that we require at least 124 patients in each group. Taking into account 10% attrition (refusal after randomisation-based on the results of our pilot survey) and 30 % loss at the endpoint (based on trials in this area - range 2-30%) [21] we will need to recruit 207 participants in each group.

Sample size was also calculated on the outcome measure oral health status using the assumption that 50% of pregnant women in the control group will have gingival bleeding (based on trials in this area) [21]. A 30% improvement in oral health status is expected in IG1 and IG2 (30% reduction in gingival bleeding). To detect a difference of at least 30% between the groups with a two-sided test of proportions, alpha of 0.017, and 80% power we determine using statistical software [45] that we require at least 52 patients in each group. Taking into account 10% attrition and 30 % loss at the endpoint we will need to recruit 87 participants in each group. Based on these estimations we will require a total of 621 participants for the trial (207 in each group). Interim analyses will be used to re-check the sample size after the first 100 women are recruited.

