### Data analysis

Per-protocol and intention-to-treat analysis will be conducted by staff blinded to the group allocation. Missing data will be coded in the database structure and handled using an appropriate method. Demographic data will be analysed using descriptive statistics. All variables will be examined for normality and appropriate data transformations will be applied. Potential confounders (income, pre-existing oral health conditions, and others) and the impact of the MIOH/MIOH-DS intervention will be examined using univariate and multivariate methods. Regression analysis that take into account the variables of interests to the outcome will be performed. Some of the variables will be considered as exerting fixed effects (e.g. the number of patient groups) while others as random effects e.g. oral health knowledge. The regression models will also include a hospital variable (1–3). Analysis will be conducted for each hospital clinic and if no differences are found, data will be pooled. Pearson’s Chi-square test will be used to analyse the proportion of pregnant women accessing dental services. Oral health status and knowledge outcomes will be analysed using Analysis of Variance and post-hoc procedures. The effectiveness of the oral health education program will be assessed using dependent t-tests.

The sensitivity and specificity of the oral assessment tool using the OHIP-14 as the gold standard will be calculated using odds ratios. For this analysis the total scores using the midwifery oral assessment tool for participants in IG1 and IG2 will be dichotomised as 0=0 (no risk) and 1 to 2=1 (at risk). The total scores for participants using the OHIP-14 in IG1 & 2 will also be dichotomised using the median split as described by Locker et al. [42]. Subjects with an OHIP-14 score of 0–7 will be scored 0 (no risk) and 8–56 a score of 1 (at risk). Sensitivity and specificity will also be calculated using the initial dental oral assessment in IG2 as the gold standard. Analysis of proportions using chi square procedures (two tailed) and confidence intervals will be undertaken to determine sensitivity (true positives), specificity (true negatives), false positives, false negatives, negative and positive predictive values [46].

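### The rule to pool hospitals only if they do not differ conflicts with the single pooled comparison the trial was sized for, and its cost ranges from slight to severe depending on what "differences" means

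*Protocol article*

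**What the plan says.** **Data analysis.** The section sets a conditional rule: "Analysis will be conducted for each hospital clinic and if no differences are found, data will be pooled". It gives no meaning for *differences*, and no test or threshold. For uptake it names an unstratified Pearson test: "Chi-square test will be used to analyse the proportion of pregnant women accessing dental services". The same paragraph puts a three-level hospital term in the regression models and lists pre-existing oral health conditions among the potential confounders to be examined. It does not make any regression the uptake analysis.

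**Randomisation.** Permuted blocks are used, "stratifying participants by hospital and presence of a dental problem".

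**Sample size.** The trial is sized on uptake. The control assumption is "30% of pregnant women in the control group will access dental services during pregnancy". Success is "at least 50% of the pregnant women in IG1 and IG2 will access dental services during pregnancy, a difference of 20% between the groups". The error rates are "alpha of 0.017 (three comparisons 0.05/3), and 80% power", and the conclusion is "we require at least 124 patients in each group". After allowing for losses this becomes 207 recruited per group, 621 in all. Nothing is sized for a single hospital.

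**The concern.** Uptake is part of the primary hypothesis and sets the sample size. The calculation assumes that all women in an arm are compared in one test. The Data analysis rule lets the data decide whether that test is done at all.

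One natural trigger, a difference between hospitals in how many women see a dentist, is expected and harmless. Because randomisation is stratified by hospital, the arms are balanced within each hospital, so a different uptake level does not bias the pooled comparison. If such a difference nevertheless blocks pooling, a trial of 621 women reports three small comparisons per contrast, none of them powered. The rule also sits badly with a hospital term in the regression models, which has a purpose only when the hospitals are combined.

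**Working it through.** **1. Reproduce the planned size.** Inputs from the Sample size section: p1 = 0.30, p2 = 0.50, two-sided alpha 0.017, power 80%. The mean proportion is 0.40.

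n = [z(1−α/2)·√(2·0.40·0.60) + z(power)·√(0.30·0.70 + 0.50·0.50)]² / 0.20²
= [2.387·0.6928 + 0.8416·0.6782]² / 0.04 = (1.6536 + 0.5708)² / 0.04 ≈ 123.7, so **124 per group**, as stated. (Unrounded alpha of 0.05/3 gives 125.) With combined losses of 40%, 124/0.6 = 206.7, so 207.

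**2. Power pooled and within one hospital.** Power = Φ[(0.20·√n − 1.6536)/0.6782].

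- n = 124: Φ(0.846) = **80.1%**.
- n = 41: Φ(−0.550) = **29.1%**. Here 124/3 ≈ 41 per arm per hospital; equal thirds is an assumption, since the article gives no split.
- n = 69 (207/3, no losses at all): **50.5%**.

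**3. What the rule does overall.** The rule was simulated (100,000 trials per scenario) with 41, 41 and 42 women per arm at the three hospitals and a constant gain of 20 points everywhere. The pre-test level of 5% and the hospital rates are assumptions. *Average power* is for one pairwise comparison: the pooled test when pooling is allowed, and the mean of the three single-hospital tests when it is not.

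| Control uptake by hospital | Meaning of *differences* | Pooling blocked | Average power | Always pooled, unstratified | Always pooled, stratified by hospital |
|---|---|---|---|---|---|
| 30/30/30% | treatment effect | 5.9% | 78.1% | 80.3% | 80.2% |
| 20/30/40% | treatment effect | 5.9% | 78.2% | 80.4% | 81.2% |
| 15/30/45% | treatment effect | 5.8% | 78.7% | 80.9% | 83.2% |
| 30/30/30% | uptake level | 4.5% | 78.1% | 80.3% | 80.2% |
| 20/30/40% | uptake level | 65.2% | 49.4% | 80.4% | 81.2% |
| 15/30/45% | uptake level | 96.1% | 35.5% | 80.9% | 83.2% |

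The uptake-level test above uses the two arms being compared. With all three arms (124 women per hospital), overall uptake of 33/43/53% triggers a 5% test 82% of the time, and 38/43/48% triggers it 28% of the time.

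**4. The unstratified test taken alone.** Over six strata (hospital by dental problem), with assumed spreads of 0 to 20 points between dental-problem strata and 0 or 10 points between adjacent hospitals, the crude test had 80.3–81.3% power and the stratified test 80.2–83.8%. The crude type I error was 1.3–1.75% against a nominal 1.7%. The cost is therefore about 0–3 points of power, with mild conservatism.

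**The case against.** The best defence is that the sentence can mean differences in the hospital-specific results, that is, in treatment effect. On that reading, with a constant true effect, pooling is blocked about 6% of the time and about two points of power are lost. This stands as a possible reading, and it is why the cost must be given as a range.

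A second defence is that the article is condensed, so the test and threshold may be in an analysis plan that is not shown. That is fair for those details, and their absence is not the point. The rule itself is stated, and nothing elsewhere in the article withdraws it.

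Three stronger readings are tempting, and the document does not support them:

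- A reader might infer that the trial's power is 29%. That is the power of one comparison in one hospital once pooling has been refused, under equal thirds and the full 40% loss. The article cites a range of 2–30% for endpoint loss, so it has planned at the upper end.
- A reader might blame the unstratified chi-square for the fall in power. Step 4 shows that it is valid and costs little.
- A reader might conclude that the multicentre result is abandoned or the dental-problem stratum ignored. The hospital term in the regression models implies combined data, and pre-existing oral health conditions are listed as a potential confounder. Neither, however, is tied to the uptake analysis.

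**Conclusion.** The point holds as a conflict within the protocol. The pooling rule contradicts the single pooled comparison behind the 124 per group, gives no weight to stratification by hospital, and fits poorly with the hospital term in the regression models.

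Its size depends on an undefined word. Under the treatment-effect reading with a constant effect, average power is about 78–79%. Under the uptake-level reading it is about 49% when control uptake is 20/30/40%, and about 36% at 15/30/45%. If the hospitals are truly alike, it is about 78% on either reading. These figures rest on an assumed 5% pre-test, equal thirds and hypothetical hospital rates.

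The unstratified uptake test is a secondary matter of efficiency.

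**What to change.** Delete the conditional-pooling sentence. Pre-specify one pooled uptake analysis, stratified by or adjusted for hospital and presence of a dental problem, for example a Mantel-Haenszel risk difference or a logistic regression with both factors. Put the same two factors in the models for oral health and knowledge. Report hospital-specific effects and the hospital-by-arm interaction as secondary, with no bearing on whether the data are pooled.

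The cost is wording only. Both factors are already recorded for randomisation, and the stratified analysis keeps about 80–84% power with the existing 124 per group in the scenarios tried. The change should be made before any unblinded analysis.

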### Participants and recruitment

Participants are being recruited from antenatal clinics across three large metropolitan hospitals in Greater Western Sydney, Australia. Information about the study is provided to all pregnant women attending their first antenatal visit (booking visit). At all Australian antenatal clinics the first booking visit is attended by midwives. While waiting to see the midwife, pregnant women are invited to participate by an independent recruiter (dental assistant). Women are eligible for recruitment (inclusion criteria): if they are more than 18 years of age; do not have cardiac disease that would warrant the need of antibiotics for dental treatment; have not received dental treatment in the current pregnancy; have a single pregnancy of more than 12 and less than 20 weeks of gestational age; do not have any known foetal anomalies or other risk factors (including history of preterm birth) that would place the pregnancy at risk of complications; and are able to attend regularly for dental treatment if required. Informed written consent is obtained by the dental assistant from pregnant women who meet the study inclusion criteria.

A self-administered pre-questionnaire is then provided to obtain baseline demographic data, dental/medical aspects of the women’s health (such as uptake of dental services, quality of oral health) and pre-test oral health knowledge. In addition, the Oral Health Impact Profile-14 (OHIP-14) questionnaire will also be administered. The OHIP-14 is a subjective measure of oral health that has been used extensively and found to be a precise, valid and reliable instrument (α=0.88) [27, 28]. It contains 14 questions assessed on a 5-point Likert scale and the total scores range from 0–56 with higher scores indicating poorer oral health. The OHIP-14 assists in validation and determining the sensitivity and specificity of the midwifery oral assessment tool by representing the ‘gold standard’ for identifying participants at risk of having oral health problems. Participants from non-English speaking backgrounds are provided, if required, interpreter services and translated oral health promotional materials.

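### Uptake, the outcome that sizes the trial, is tied only to an unadjusted chi-square; the planned covariate regression is not linked to it, so available baseline precision is not secured

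*Protocol article*

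**What the plan says.** All references are to the protocol article.

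- **Sample size.** "Sample size estimation is calculated on the outcome measure uptake of dental services". The assumptions are that "30% of pregnant women in the control group will access dental services during pregnancy" and that the intervention succeeds with "at least 50% of the pregnant women in IG1 and IG2 will access dental services during pregnancy, a difference of 20% between the groups". The test is a "two-sided test of proportions, alpha of 0.017 (three comparisons 0.05/3), and 80% power", and the result is that "we require at least 124 patients in each group". Recruitment is raised to 207 per group for 10% attrition and 30% endpoint loss.
- **Participants and recruitment.** A self-administered pre-questionnaire collects demographic, dental and medical items, "such as uptake of dental services, quality of oral health) and pre-test oral health knowledge". OHIP-14 is also given. Women who have already had dental treatment in this pregnancy are not eligible.
- **Randomisation.** Allocation follows baseline data collection and is stratified by hospital and presence of a dental problem.
- **Data analysis.** For uptake, Pearson's "Chi-square test will be used to analyse the proportion of pregnant women accessing dental services". Separately, confounders (income, pre-existing oral health conditions and unspecified others) and the intervention's impact are to be examined by univariate and multivariate methods. Regression models with a hospital term are planned, but no outcome is named for them.

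**The concern.** The section that fixes the analysis names one test for the sizing outcome, and that test cannot use a covariate. It matches the test of proportions used for the sample size, so it reads as the confirmatory analysis. The regression text could also cover uptake, but it is attached to no outcome and is given no rank against the chi-square.

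Two things are at stake. First, covariates that predict attendance would sharpen the estimated risk difference and correct chance imbalance between arms, using data collected before allocation. The two stratification factors are the best documented of these, and the named test uses neither. Second, with two candidate analyses and no stated order, the choice could be made after the results are seen.

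**Working it through.** **Inputs.** From Sample size: p1 = 0.30, p2 = 0.50, difference 0.20, two-sided alpha 0.017 (0.05/3), power 0.80, 124 evaluable and 207 recruited per group. Not in the article: rho, the within-arm correlation between the baseline covariates and uptake. It is assumed here over 0 to 0.4.

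**Step 1: the plan's own figure.** With mean proportion 0.40:

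n = [z(1−α/2)·√(2·0.40·0.60) + z(0.80)·√(0.30·0.70 + 0.50·0.50)]² / 0.20²

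At alpha 0.017, z = 2.387, so n = [2.387·0.6928 + 0.8416·0.6782]² / 0.04 = 123.7, which rounds up to 124. This matches. Unrounded 0.05/3 gives 125. For recruitment, 124/(1 − 0.40) = 206.7, which rounds up to 207. This also matches.

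**Step 2: power of the unadjusted test at 124 per group.**

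Power = Φ{[0.20·√124 − z·0.6928] / 0.6782}

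This gives 80.1% at alpha 0.017. At 0.05/3, z = 2.394, the bracket is 2.227 − 1.659 = 0.568, and 0.568/0.6782 = 0.838, so power is 79.9%.

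**Step 3: power with adjustment.** Adjustment reduces the variance of the risk difference by a factor of about 1 − rho², so 124 acts like 124/(1 − rho²). At alpha 0.05/3:

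| Assumed rho | 1 − rho² | Effective n per group | Power | Gain (points) |
|---|---|---|---|---|
| 0 | 1.00 | 124 | 79.9% | 0 |
| 0.2 | 0.96 | 129 | 81.8% | 2 |
| 0.3 | 0.91 | 136 | 84.1% | 4 |
| 0.4 | 0.84 | 148 | 87.2% | 7 |

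**Step 4: what such values of rho would mean.** Suppose half the controls were earlier attenders. Then rho = 0.5 × gap / √(0.30·0.70). Uptake of 40% against 20% gives 0.5·0.20/0.458 = 0.22. Uptake of 45% against 15% gives 0.33. Both splits are illustrations and are not in the article.

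**Step 5: if the intervention weakens the link.** Step 3 takes the same association in both arms. IG2 refers every woman, with a voucher for free priority care, which may loosen the link with past attendance. Simulations (20,000 trials, 124 per arm, adjusted risk difference with robust standard error, 30-point control gap) gave power 0.846 with an equal gap in the intervention arm, 0.833 with a 15-point gap and 0.818 with none. Chi-square power was about 0.80 throughout. A little of the simulated gain comes from the standard error rather than the covariate: an unpooled variance alone needs 120 per group instead of 124 at alpha 0.017.

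**Step 6: what the baseline uptake item can carry.** The sized outcome is attendance during this pregnancy, and women already treated in it are excluded. The baseline value of that outcome is therefore nearly constant; a check-up without treatment may leave slight variation. The item can predict later uptake only as far as it records earlier attendance, and the article does not give its recall period. Self-rated oral health and OHIP-14 are not restricted in this way.

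**The case against.** The strongest reply is that nothing here is wrong. The chi-square is a valid test in a randomised trial and is the one the trial was sized for. Multivariate methods, a hospital term and an open covariate list are already planned. The full covariate list and the estimator normally belong in a statistical analysis plan, which is not shown, and the gain rests on a correlation the article does not report.

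Most of this stands. The absence of a covariate list is not the point. The point rests on what the article does fix: one unadjusted test for the sizing outcome, and regression with neither an outcome nor a rank.

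A reader might go further in four ways that the article does not support:

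- **That precision is discarded.** The planned regression could recover it; it is only not secured.
- **That the outcome itself was measured at baseline and would predict strongly.** Eligibility makes that value almost constant. A rho as high as 0.5 has no source in the article; with half the controls earlier attenders it would need control uptake of about 53% against 7%.
- **That uptake has no spare power.** This holds only if the full 40% is lost. The cited endpoint range is 2–30%, and uptake is also taken from clinic databases, returned checklists and contact with dentists. With 30% total loss (207 × 0.70 ≈ 145 per group) unadjusted power is about 87%; with 12% (207 × 0.88 ≈ 182) it is about 94%.
- **That past attendance is the main determinant of attending.** The Background points to access, cost, waiting lists and beliefs about safety.

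**Conclusion.** The concern holds as a gap in specification with a modest, uncertain cost in efficiency. The primary analysis of uptake is not fixed between an unadjusted chi-square and an unassigned regression, and the test actually named uses neither the stratification factors nor any baseline predictor.

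The gain from adjustment runs from about nil to 7 points of power over rho 0 to 0.4, with 2 to 4 points at rho 0.2 to 0.3, and less where the intervention loosens the link with past attendance. All of these rest on an assumed rho and on exactly 124 evaluable women per group. It would be wrong to infer that the trial is underpowered or its result invalid: 124 and 207 reproduce from the stated inputs.

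**What to change.** In Data analysis, name one primary analysis of uptake for each pair of arms: logistic regression standardised to a risk difference, with a robust standard error, at the alpha already allotted. Include as pre-specified covariates:

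- hospital and presence of a dental problem, as used in the randomisation;
- baseline self-rated oral health;
- earlier dental attendance, if the pre-questionnaire item records it. Check its wording and recall period before listing it.

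OHIP-14 is also available, if the sponsor prefers it as a further measure of baseline oral health. Keep the chi-square as an unadjusted sensitivity analysis.

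The cost is a few sentences and minor programming. No new data, no additional women and no change to the sample size are needed. The small downside is that missing baseline items need a simple rule stated in advance, such as a missing-indicator category.

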##### Intervention group 2 (IG2)

This group receives oral health promotional material at the time of recruitment. This group also receives a **midwifery and dental intervention** (MIOH-DS). The **midwifery intervention** will be similar to Intervention group 1. However, in this group all pregnant women, regardless of whether they are assessed to be at risk of having dental problems or not by the midwife, are referred (referral letter with checklist) to the dentists employed for this study for an initial dental oral assessment (part of the dental intervention). This allows for further testing of the midwifery oral assessment tool and to gather baseline oral health data. Pregnant women who consent are provided vouchers that entitle them to priority access to free oral assessment and treatment by the study dentists at dental clinics in the recruitment hospitals. This service is an extra service created specifically for this study and is co-ordinated by the study team. The voucher is valid for 4 weeks from booking visit date to encourage pregnant women to see the dentist promptly. Pregnant women can make the dental appointment by calling the telephone number provided with the referral letter or contacting the dental assistant in the antenatal waiting room.

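### The dentist reference for the midwife tool exists only for IG2 women who attend, so direct sensitivity and specificity are biased if attendance follows the tool result

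*Protocol article*

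**What the plan says.** The Outcome measures section of the protocol article lists the accuracy of the two-question midwife tool as an outcome, with two references. One is the OHIP-14 questionnaire, completed at recruitment and used in IG1 and IG2. The other is the first examination by the study dentists, used in IG2 only. For the second, Data analysis states: "Sensitivity and specificity will also be calculated using the initial dental oral assessment in IG2 as the gold standard".

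The section on Intervention group 2 explains how that examination comes about. All IG2 women, "regardless of whether they are assessed to be at risk of having dental problems or not by the midwife, are referred" to the study dentists, and one stated reason is the tool: "This allows for further testing of the midwifery oral assessment tool and to gather baseline oral health data". Attendance is then up to the woman. "Pregnant women who consent are provided vouchers that entitle them to priority access to free oral assessment and treatment", and "The voucher is valid for 4 weeks from booking visit date". She books by telephone or through the dental assistant in the antenatal waiting room.

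Data analysis goes on to chi-square procedures and confidence intervals for sensitivity, specificity, error rates and both predictive values. On missing data it gives only a general undertaking to code it and handle it suitably. Nothing there concerns IG2 women who have a tool result but no dentist examination.

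**The concern.** A woman who is not examined has no reference result, so a direct calculation can use only those who came. Whether she comes may depend on what the midwife found. A tool-positive woman has usually voiced a concern herself and has then been identified as at risk. A tool-negative woman has less reason to use the voucher. The Discussion section itself expects referral by midwives to encourage dental attendance.

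This is partial verification. If unexamined women are disproportionately tool-negative, two things are lost from the table: missed cases, which makes the tool look more sensitive than it is, and true negatives, which makes it look less specific. The dentist examination is the only clinical reference, since OHIP-14 is self-reported. In IG1 the tool helps decide who is referred, and the authors foresee translation into guidelines. An inflated sensitivity would hide women whom the tool misses.

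**Working it through.** **The plan's own figures.** The documents give no sensitivity, specificity or attendance by tool result. The nearest figure is the uptake assumption in Sample size: 30% in control against 50%, two-sided alpha 0.017, power 80%. The pooled-variance formula without continuity correction gives n = (2.387 × √(2 × 0.4 × 0.6) + 0.842 × √(0.3 × 0.7 + 0.5 × 0.5))² / 0.20² = 124 per group. Allowing 40% loss, 124 / 0.60 = 207. Both match the article.

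The criterion in that section is "at least 50% of the pregnant women in IG1 and IG2 will access dental services during pregnancy". It is a minimum for calling the intervention successful, it is set for both arms together, and it covers dental services in general. If it did apply to this examination, 0.5 × 207 ≈ 104 IG2 women would be examined, or 0.5 × 0.9 × 207 ≈ 93 after 10% refusal. These counts are illustrative only, and the bias below does not depend on them.

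**Formulas.** Let a1 and a0 be attendance among tool-positive and tool-negative women, and let attendance depend only on the tool result.

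- Apparent sensitivity = Se·a1 / (Se·a1 + (1 − Se)·a0)
- Apparent specificity = Sp·a0 / (Sp·a0 + (1 − Sp)·a1)

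Dividing through by a0 shows that only the ratio a1/a0 matters.

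**Results with assumed true Se = Sp = 70%:**

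| Attendance, tool-positive v tool-negative | Apparent sensitivity | Apparent specificity |
|---|---|---|
| 50% v 50% | 70.0% | 70.0% |
| 55% v 45% | 74.0% | 65.6% |
| 90% v 70% | 75.0% | 64.5% |
| 60% v 40% | 77.8% | 60.9% |
| 90% v 60% | 77.8% | 60.9% |
| 70% v 30% | 84.5% | 50.0% |
| 40% v 60% | 60.9% | 77.8% |

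For 60% v 40%, sensitivity is 0.42 / (0.42 + 0.12) = 0.778 and specificity is 0.28 / (0.28 + 0.18) = 0.609. For 90% v 60%, they are 0.63 / (0.63 + 0.18) = 0.778 and 0.42 / (0.42 + 0.27) = 0.609. High overall attendance does not help unless the two rates come close together.

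Other assumed true values show the same pattern at 60% v 40%: 60%/80% becomes 69.2%/72.7%, and 80%/50% becomes 85.7%/40.0%.

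**When attendance depends on disease instead.** Take Se = Sp = 0.70, prevalence 50%, and attendance of 65% if diseased and 35% if not (all assumed).

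- Examined fractions: tool-positive diseased 0.35 × 0.65 = 0.2275; tool-positive healthy 0.15 × 0.35 = 0.0525; tool-negative diseased 0.15 × 0.65 = 0.0975; tool-negative healthy 0.35 × 0.35 = 0.1225.
- Attendance by tool result: 0.28 / 0.50 = 56% v 0.22 / 0.50 = 44%.
- Direct sensitivity: 0.2275 / 0.325 = 0.70. Direct specificity: 0.1225 / 0.175 = 0.70. There is no bias, although attendance differs by tool result.
- Begg-Greenes uses P(disease | positive) = 0.2275 / 0.28 = 0.8125 and P(disease | negative) = 0.0975 / 0.22 = 0.443. With half the women tool-positive, it gives 0.8125 / (0.8125 + 0.443) = 0.65 and 0.557 / (0.557 + 0.1875) = 0.75. Here the correction itself is biased.

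The condition that matters is therefore whether attendance differs by tool result among women of the same disease status.

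**The case against.** The strongest reply is that the design already deals with the usual cause of verification bias by referring every IG2 woman. It also makes attendance easy: care is free and has priority, clinics are at the recruitment hospitals, booking is possible in the waiting room, and eligibility requires being able to attend for treatment. Attendance could be high. This stands as far as selection at referral goes, but attendance remains voluntary and time-limited, and a high overall rate leaves the bias unchanged if the ratio persists.

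A reader might infer that about half of IG2 will lack a reference result. The documents do not support that, because the 50% is a minimum for success in both arms and for dental services generally. Nor do they support saying that the estimates will be biased, since they give no attendance by tool result. It would also be wrong to say that bias is absent only when attendance is equal in tool-positive and tool-negative women: attendance driven by disease alone leaves the direct estimates correct.

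It can also be said that missing reference results are covered by the general missing-data sentence, or by an analysis plan not shown. The article does not state that unexamined women are left out, and brevity alone would be no finding. But the calculation it describes is the direct one, and that is the calculation exposed to this bias.

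Finally, tool accuracy is not part of the primary hypothesis, and the OHIP-14 comparison does not depend on dental attendance. Both points are correct and limit the consequence.

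**Conclusion.** The point holds in conditional form. Among IG2 women the dentist reference is available only for those who attend. If tool-positive women attend more often at the same disease status, which is plausible, direct sensitivity is too high and direct specificity too low. With true values of 70% each and attendance depending on the tool result alone, a ratio of 1.5 shifts them to about 78% and 61%. The milder 55% v 45% split gives about 74% and 66%. The reverse attendance pattern would reverse the direction.

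The true accuracy and the attendance splits are assumptions, not figures from the documents. Neither the direct nor the corrected estimate is right under every attendance mechanism, so neither should stand alone. The effect is confined to the validation of the tool against the dentist examination.

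**What to change.** In Data analysis, after the sentence on the IG2 dentist reference, add the following:

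- Report attendance at the initial dental assessment by tool result.
- Beside the direct estimates, give verification-corrected sensitivity and specificity for all IG2 women with a tool result. Use Begg-Greenes, or inverse-probability weighting on tool result, baseline OHIP-14 and baseline self-rated oral health. The denominator should not be all randomised IG2 women: randomisation precedes the midwife's assessment and 10% refusal afterwards is allowed for, so some may have no tool result.
- State the assumption that attendance is unrelated to disease given those variables, and add a sensitivity analysis for departures from it.
- Keep the planned predictive values. If attendance depends only on the tool result they are unbiased, and Begg-Greenes is built from them.

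The cost is one paragraph and a little programming, with no new data collection. Intervals will be slightly wider and the reported sensitivity may be lower. The randomised comparisons do not change.
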